### The SIPP intervention

SIPP is a structural intervention. That is, an intervention that promotes the availability, accessibility or acceptability of specific resources needed for specific health outcomes [37]. It is informed by comparable interventions, harm reduction principles and models of community mobilisation evidenced to have impact in diverse contexts [38, 39]. The SIPP intervention was co-produced by the team with input from people who use crack and service providers and will be delivered at study intervention sites for a period of six months.

It consists of three components:The SIPP KIT: The SIPP kit adheres to best practice guidance for provision of safe crack inhalation equipment [32]. It comprises a straight stem borosilicate glass pipe; 2 × steel gauze filters/meshes; 2 × plastic mouth pieces; and a wooden push stick, contained within a discrete hard plastic case. A brief harm reduction leaflet with instructions and a card providing information about the research study are provided with each kit (see Fig. 2)SIPP Provider Training: Informed by an evidence review, workshops with providers of specialist services for people who use drugs, and peer/stakeholder review, we developed an online training module aimed at service providers. This provides background information on crack (drug properties, use in the UK context); associated health harms and harm reduction advice; homemade pipes, suspension devices (ash, wire wool) and risk; client engagement tips; SIPP kit use and provision. Training evaluation and participant registration details are embedded within the platform.Peer-2-peer harm reduction: Brief verbal harm reduction messaging to support SIPP kit provision. With peers (i.e. people who use crack) we developed a hierarchy of harm reduction messages that can be tailored to suit an individual's specific information requirements and time available. The development and provision of this messaging is an iterative process, informed by feedback from peer researchers on local participant needs and contexts of delivery.

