### Study partners and sites

The SIPP study would not be possible without the support of local police forces, specialist drug service providers, community members and charity organisations working to support peer advocacy and involvement. Prohibition of crack pipe provision necessitated contact with local Chief Constables and Police and Crime Commissioners prior to study site selection. Our intervention sites in Bristol, Nottingham, and Mansfield, are under the jurisdiction of the Avon & Somerset Police and the Nottinghamshire Police, respectively. Both have provided written approval for SIPP kit distribution through our specialist drug service providers and peer-network partners for the six-month duration of the intervention.

Non-equivalent control sites have been selected for intervention site comparability, with attention to local geography, demographics and the number of people using specialist services for drug use type recorded as using crack cocaine. Geographical distance between control and intervention sites decreases contamination risk. The control sites are: Birmingham (for Bristol, conurbations); Coventry (for Nottingham, mid-sized cities); Leamington Spa and Nuneaton in Warwickshire (for Mansfield, Nottinghamshire, peri-rural/rural sites adjoining Coventry and Nottingham, respectively). Each intervention and control site has a primary partner who is specialist provider of services for people who use drugs, with additional peer network and outreach distribution supported by Coact (Bristol), The Hepatitis C Trust (Birmingham) and POW sex worker support service and outreach (Nottingham). See Table 2, below.

**Table 2 Tab2:** Intervention and non-equivalent control sites

Service type	Intervention site	Non-equivalent control site
Specialist drug service	Nottingham Health Shop/Well-being Hub	Change Grow Live—Coventry
Sex worker support service	POW Nottingham	
Specialist drug service	Bristol Drugs Project	Change Grow Live—Birmingham west
Peer network	Bristol COACT peer activist group	Hepatitis C Trust peer outreach—Birmingham
Specialist drug service	Change Grow Live –Nottinghamshire	Change Grow Live—Warwickshire

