##### Analysis

We will analyse quantitative data in four ways. Firstly, we will describe demographic characteristics, drug use behaviours, and indicators of social exclusion among PWUC stratified by exposure group at the pre- and post-survey time points. Secondly, we will estimate the change in primary outcome (sharing of pipes in past 28 days) for participants in intervention sites compared to control sites. Logistic regression will be used to compare baseline prevalence of primary and secondary outcome measures between intervention and control sites post-intervention. Primary analysis will use an adjusted, individual-level intention-to-treat approach, including all participant data (irrespective of baseline and follow-up participation, their engagement with SIPP and assuming missing observations are missing at random) in order to reflect the effects of SIPP in every day practice. The same analysis plan will be used for secondary outcomes (use of homemade pipes, cuts/burns, injecting, and service engagement). Linear regression models will compare baseline frequency of injecting between intervention and control sites and estimate relative changes in mean frequency of injecting. Logistic and linear models will adjust for a priori confounders including sex, age, duration of crack use, engagement in services, primary outcome measures, and any variables with evidence of imbalance described above. As a sensitivity analysis will focus on participants for which we have baseline and follow-up (though data linkage) to assess changes in outcomes over time and between intervention and control. Thirdly, we will undertake a per-protocol analysis, limiting the analyses to participants with both baseline and follow-up data and who report use of SIPP. This will give a measure of efficacy where SIPP is delivered in the optimal way.

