Appropriate statistical models will be selected based on evidence of clustering observed. The model will include fixed effects for time and treatment, and we will explore the appropriateness of including a random effect to account for heterogeneity of participants within sites or a fixed effect to account for heterogeneity across sites. We will explore the need to adjust for clustering within treatment site and by sites using intra-class correlation coefficients. Fourthly, we will examine evidence of a dose–response relationship between intensity of exposure to SIPP and primary and secondary outcomes using logistic regression models and categorising exposure to SIPP as a continuous or categorical variable (1, 2–3, 4–5,6 + exposures) depending on the distribution of contacts with SIPP in the intervention sites.

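### As written, the per-protocol analysis loses essentially all linked controls, and its efficacy label is unsupported even if controls are kept

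*Protocol article*

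**What the plan says.** The Analysis section under Impact evaluation describes three analyses that bear on this point.

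- The primary one is controlled: "Primary analysis will use an adjusted, individual-level intention-to-treat approach, including all participant data".
- A sensitivity analysis takes participants linked across the two surveys "to assess changes in outcomes over time and between intervention and control", so it is controlled too.
- Then comes the per-protocol analysis: "we will undertake a per-protocol analysis, limiting the analyses to participants with both baseline and follow-up data and who report use of SIPP". It is interpreted at once: "This will give a measure of efficacy where SIPP is delivered in the optimal way". No comparator is named and there is no separate rule for control participants.

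The section on the SIPP intervention says that SIPP "will be delivered at study intervention sites for a period of six months". Study partners and sites adds: "Geographical distance between control and intervention sites decreases contamination risk".

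The Analysis section goes on to specify fixed effects for time and treatment. It also plans a dose-response analysis relating "intensity of exposure to SIPP and primary and secondary outcomes using logistic regression models", with exposure either continuous or in categories that start at 1.

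**The concern.** Both conditions of the per-protocol set are placed on participants in general, and control participants have no SIPP to report. Read literally, the set contains intervention-site users only. The estimate is then their change over time, and anything else that moved pipe sharing between the surveys is included in it. The protocol expects that such things may happen: in the process evaluation, qualitative work is meant to give insight into secular changes at intervention sites.

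The label adds to the problem. Reporting use sets no minimum exposure, although the dose categories run from 1 to 6 or more, and the intervention has three components. Use is also chosen by the participant after baseline.

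The Background faults earlier studies as mostly observational and uncontrolled, and presents the control sites as this study's answer to that. An uncontrolled figure called efficacy would return to the weaker design, in a study whose findings are meant to inform legislative review.

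**Working it through.** **Inputs from the protocol article (Sample size).** 52% v 32% sharing, 90% power, significance 0.05, 204 SIPP and 102 control, inflated to 500 and 240, with 75% linkage.

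**Inputs assumed, because the article gives no figure.** Uptake u among linked intervention participants, 0.3 to 1.0; a background fall in sharing of 5 or 10 points; within-person correlation ρ of 0 to 0.4.

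**Step 1: the plan's own figure.** With r = 2 and pooled proportion p̄ = (0.52 + 2 × 0.32)/3 = 0.3867, the two-sided size for the control group is

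n = [1.96 √(1.5 × p̄(1 − p̄)) + 1.2816 √(0.52 × 0.48 + 0.32 × 0.68/2)]² / 0.20² = 93.7, so 94.

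The continuity correction, n/4 × [1 + √(1 + 2(r + 1)/(r n × 0.20))]², gives 101.1, so 102. Hence 102 + 204 = 306, an exact match. The sample size is not at fault.

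**Step 2: who is left in the per-protocol set.**

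- Linked participants: 500 × 0.75 = 375 SIPP and 240 × 0.75 = 180 control.
- Kept by the rule as written: 375 × u users, which is 112 at u = 0.3 and 375 at u = 1.0, and none of the 180 controls apart from any contaminated ones.
- With no controls the treatment term is constant, so a treatment effect cannot be separated from time.

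**Step 3: what background change does in that set.** Suppose SIPP has no effect and u = 0.5, giving 188 users. The variance of the before-after difference is [p₀(1 − p₀) + p₁(1 − p₁) − 2ρ√(p₀(1 − p₀)p₁(1 − p₁))]/188, and the chance of a significant fall is Φ(fall/SE − 1.96).

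| Assumed fall | ρ = 0 | ρ = 0.4 |
|---|---|---|
| 5 points (52% to 47%) | 16% | 24% |
| 10 points (52% to 42%) | 50% | 71% |

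For the 10-point fall with ρ = 0: variance = (0.2496 + 0.2436)/188 = 0.00262, SE = 0.0512, and Φ(1.952 − 1.96) = 0.497. The point estimate itself is wrong by the whole background change.

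**Step 4: the other reading, with controls kept.** Suppose again that SIPP has no effect and that all linked intervention participants change on average as controls do. That average is u × (change in users) + (1 − u) × (change in non-users). Users minus controls is therefore (1 − u) × (change in users − change in non-users). At u = 0.5 half of any user/non-user difference enters the estimate, and at u = 0.3 it is 70%. The article gives no figure for that difference, so the bias has no known size or sign, but nothing in the per-protocol text removes it.

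**Step 5: whether numbers force the controls out.** With 180 linked controls kept, unadjusted power for 52% v 32% without continuity correction is 92.5% at u = 0.3, 97.5% at 0.5, 98.9% at 0.7 and 99.5% at 1.0. These figures ignore site clustering and selection into use. Sample size gives no reason to drop the controls.

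**The case against.** The best defence is that the sentence is merely compressed. It follows two analyses that compare intervention with control, and the text then specifies a model with a treatment term, which needs controls. On that reading the use condition defines adherence at intervention sites and linked controls remain. This is plausible, and it rules out saying that the investigators certainly intend a single-arm analysis. But the article does not say so, and step 4 shows that the label fails on that reading as well. Nor is this a detail left to an analysis plan that is not shown: the article fixes both the population and its interpretation.

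Some stronger inferences are tempting but unsupported:

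- That the study throws away its control sites. It does not; the primary and linked sensitivity analyses keep them.
- That the per-protocol figure is the one policy makers will see. The article speaks only of findings in general.
- That regression to the mean is built in. Eligibility is recent crack use, not high baseline sharing, and nothing shows that users would be selected on sharing.
- That the number of SIPP contacts reflects how much crack a person smokes. No section says so. The exposure variable may also be continuous, which need not exclude zero, and the dose-response result is not called efficacy.

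A complier-average estimate is not a clean substitute either. Take an assumed 12-point intention-to-treat difference and 60% uptake: 12/0.60 = 20 points among users. If non-users also fell by an assumed 5 points, the figure is (12 − 0.4 × 5)/0.6 = 16.7. Such spillover is plausible for a structural intervention with provider training and peer messaging. The sites are not randomised, and distance is said to lower contamination, not to remove it.

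**Conclusion.** The point stands for one supplementary analysis. As written, the rule removes essentially all of about 180 expected linked controls and credits any background change to SIPP. If controls were meant to stay, self-selected users would be compared with unselected controls. Neither reading supports calling the result efficacy under optimal delivery.

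The count of 180 rests on the stated sample and linkage and on little or no contamination. The 16% to 71% chances of a spurious result rest on assumed falls of 5 to 10 points, 50% uptake and correlations of 0 to 0.4, and they apply only to the literal reading. The primary result is untouched. The change is worth making because it is cheap and removes an avoidable bias, but it does not call the main design into question.

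**What to change.** - Apply the SIPP-use condition to intervention-site participants only, and keep all linked control participants as the comparator.
- Estimate the group-by-time contrast, adjusted for the baseline outcome and for baseline predictors of SIPP use.
- Replace the sentence on efficacy and optimal delivery with a statement that this is a non-randomised association among users, open to selection into use.
- Optionally, add a complier-average estimate as a sensitivity analysis. State its assumptions (no effect on non-users, parallel trends between sites) and use the control uptake actually observed instead of presuming zero.
- Describe the dose-response result as an association. Adding a zero-contact category and adjusting for pre-survey frequency of crack use are optional.

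The cost is some wording, slightly more analysis on participants already in the planned sample, and a more modest label. No extra recruitment is needed.

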**Fig. 1 Fig1:**
[figure not shown]
SIPP logic model

We employ a mixed-methods quasi-experimental design to examine whether, to what extent and how SIPP acts to reduce health risks and enhance service engagement among people who use crack cocaine. Objectives, detailed in Table 1, will be achieved through the implementation of: (1) peer-network capacity building and co-production; (2) an impact evaluation comprising a pre- and post-intervention survey with a non-equivalent control group; (3) a process evaluation comprising ethnographic observations, qualitative interviews and monitoring data; (4) an economic evaluation. Detail on each study component is provided below, after a brief outline of the SIPP intervention and study sites.

**Table 1 Tab1:** SIPP study objectives and components

SIPP objective	Study component
1. Build peer-network research capacity and explore whether the quality and impact of their SIPP engagement with PWUC differs in comparison with SIPP engagement through drug treatment services	Peer network
	Process evaluation; Impact evaluation
2. Measure the effect and cost-effectiveness of the SIPP kit on harms and risks associated with crack use (pipe sharing, presentation at drug services, using homemade pipes, cuts/burns, crack injecting)	Impact evaluation; economic evaluation
3. Evaluate SIPP fidelity, reach and acceptability in diverse specialist drug service and peer-network settings	Process evaluation
4. Explore the barriers and facilitators to SIPP uptake and service engagement among PWUC	Process evaluation
5. Explore the mechanisms through which SIPP facilitates changes in health risks and access to services, and how these are shaped by local contextual factors	Process evaluation
6. Co-develop a scalable SIPP toolkit and harm reduction resources to enhance PWUC engagement with specialist drug services and to facilitate crack-related risk reduction practices	Peer network
7. Translate evidence to policy and advocacy outputs, including to inform legislative review	All components

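### The primary contrast is mis-specified for a non-equivalent pre-post design: no group-by-wave term is named, treatment is undefined, and site effects are optional

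*Protocol article*

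**What the plan says.** The section The SIPP study, below Fig. 1, describes the design as "an impact evaluation comprising a pre- and post-intervention survey with a non-equivalent control group". Sites were therefore not randomised.

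Under Impact evaluation, Analysis, the aim is given as: "we will estimate the change in primary outcome (sharing of pipes in past 28 days) for participants in intervention sites compared to control sites". That is a comparison of changes.

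The next sentence describes the comparison differently: "Logistic regression will be used to compare baseline prevalence of primary and secondary outcome measures between intervention and control sites post-intervention".

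The analysis set covers both surveys, "including all participant data (irrespective of baseline and follow-up participation" and so on. On covariates, the text says: "Logistic and linear models will adjust for a priori confounders including sex, age, duration of crack use, engagement in services, primary outcome measures", plus any variables found to be imbalanced. The same plan applies to the secondary outcomes.

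The following paragraph opens "Appropriate statistical models will be selected based on evidence of clustering observed" and then gives the model terms: "The model will include fixed effects for time and treatment". On sites it says only that "we will explore the appropriateness of including a random effect to account for heterogeneity of participants within sites or a fixed effect to account for" differences across sites.

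No time-by-treatment term is named anywhere in the article. Nor does the text say whether treatment means the site group or an exposure that begins at launch.

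**The concern.** In a non-randomised pre-post study, the pre-survey protects the answer only if the model subtracts the baseline gap between the groups. That takes a group-by-wave coefficient, or an equivalent. The listed terms do not guarantee one, and whether they supply one depends on two matters the text leaves open: what treatment means, and whether a site or group term is kept. The sentence on baseline prevalence after the intervention contradicts itself and at best describes a post-only comparison of non-equivalent sites.

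Under most readings a baseline difference between sites enters the estimate. It could appear as benefit where there is none, or hide a real benefit. The same structure serves the secondary outcomes, and the effect estimates feed the cost-effectiveness analysis and the case for legislative review.

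**Working it through.** **Inputs.** Sample size section: 52% sharing, falling to 32%; 306 participants (204 SIPP, 102 control) at 90% power and significance 0.05; inflated to 740 (500 SIPP, 240 control), allowing for 75% linkage. The abstract applies about 740 to each survey point. Assumptions made here: two-sided test, independent observations, no clustering, no covariates, control sites steady at 52%, and baseline gaps of 10 or 20 points. The protocol gives no baseline gap.

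**The plan's own figure.** Two-proportion formula at one time point, allocation k = 2, pooled proportion (0.52 + 2 × 0.32)/3 = 0.387:
- Uncorrected control n = [1.96 × √(0.387 × 0.613 × 1.5) + 1.282 × √(0.52 × 0.48 + 0.32 × 0.68/2)]² / 0.20² = 93.7, so 94 (total 282).
- With continuity correction, (n/4) × [1 + √(1 + 2(k + 1)/(n × k × 0.20))]² = 101.1, so 102 control and 204 SIPP, total 306.

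The stated 306 is reproduced exactly. It is sized for a single two-group comparison.

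**What each reading estimates.** Let L0 and L1 be the intervention-versus-control log odds ratios at the pre- and post-survey.
- A, treatment is the arm label, model with time and treatment: the coefficient is close to (L0 + L1)/2.
- B, treatment is 1 only in intervention sites after launch, no group or site term: the pre-survey groups are pooled, so the coefficient is L1.
- C, as B with group or fixed site effects, or equivalently group plus wave plus group-by-wave: the coefficient is L1 − L0, the intended contrast.

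Example for the first row below: L0 = 0 and L1 = ln[(0.32/0.68)/(0.52/0.48)] = −0.834. A gives about −0.41 (odds ratio 0.66), about half the log effect; C gives −0.834 (0.43).

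Results from logistic models fitted to expected counts, 500 and 240 per survey:

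| Intervention sites, pre to post (control 52% throughout) | A | B | C |
|---|---|---|---|
| 52% to 32%: true fall, no gap | 0.66 | 0.43 | 0.43 |
| 42% to 42%: no effect, start 10 points lower | 0.67 | 0.67 | 1.00 |
| 62% to 42%: true fall, start 10 points higher | 1.00 | 0.67 | 0.44 |
| 72% to 52%: true fall, start 20 points higher | 1.52 | 1.00 | 0.42 |

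In the no-effect row, the 95% interval under A is exp(−0.403 ± 1.96 × 0.112) = 0.54 to 0.83. Under B the standard error is √[1/(500 × 0.42 × 0.58) + 1/(240 × 0.52 × 0.48)] = 0.158, giving 0.49 to 0.91. Both exclude 1.

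**Can the covariates remove the gap?** Adjusting for the primary outcome measure requires a baseline value for each person. At the planned 75% linkage, 25% of 740, or 185 follow-up respondents, have none, yet the primary analysis keeps them.

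**Power for the intended contrast (C).** At 500 and 240 per survey, with no baseline gap, SE = √[2/(240 × 0.2496) + 1/(500 × 0.2496) + 1/(500 × 0.2176)] = 0.225. Then z = 0.834/0.225 = 3.71 and power = Φ(3.71 − 1.96), about 96%. At 204 and 102 per survey, SE = 0.347, z = 2.40, and power is about 67%.

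**The case against.** A reader might infer that the model has nothing but main effects and so contains no intervention effect at all. The documents do not support that. The text says what the model will include, not that the list is complete; the sentence stands in a paragraph about clustering; covariates are listed elsewhere; and model choice is left open. A treatment indicator that switches on at launch, with group or site effects, is a valid difference in differences, as reading C shows.

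The intended contrast is also stated as a change. The parallel sentence on injecting frequency covers a baseline comparison and then relative changes, so the odd logistic sentence is probably a drafting slip for the same pair. The linked sensitivity analysis likewise looks at change over time between groups. A condensed article may leave the full equation to an analysis plan.

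The baseline gaps are assumptions, and the most striking results (an effect hidden or reversed) depend on them and on the reading. With a 10-point higher start, for instance, reading A gives 1.00 but reading B gives 0.67.

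All of this stands as a limit on the claim. It does not remove the problem. The article names model terms and describes the comparison, and what it names does not secure its stated aim. Of the three readings only one is right whatever the baseline gap, and the step that makes it right is optional.

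**Conclusion.** The concern holds in this form: the primary contrast is mis-specified because the listed terms do not deliver the stated change comparison unless treatment is a post-launch exposure and group or site effects are included. With treatment as the arm label, the design effect of 52% to 32% is reported as an odds ratio of 0.66 rather than 0.43, with no baseline gap needed. With an assumed 10-point lower start and no effect, both the arm-label reading and the exposure reading without a site term give 0.67 with an interval excluding 1. These figures rest on independent observations without clustering or covariates. It does not follow that the trial cannot estimate its effect, or that the 306 is wrong.

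**What to change.** - Name the group-by-wave coefficient as the primary effect, in a logistic model with wave, group or site effects, and the pre-specified covariates. A post-launch exposure indicator with mandatory group or site effects is equivalent. Define treatment accordingly.
- Replace the sentence on baseline prevalence after the intervention with two: a description of the outcomes at baseline by group, and the change comparison above.
- State that the secondary outcomes use the same structure.
- Give the power for this contrast. The 306 covers a single two-proportion comparison, and the 740 was set for linkage and covariate adjustment, so neither figure was derived for the interaction.

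The cost is wording and one power statement; no new data are needed. The interaction is less precise than a single-time-point comparison, but at 500 and 240 per survey power is about 96% before clustering. An allowance for clustering by site would lower that and should be shown.

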##### Sample size

A sample of 306 (204 SIPP, 102 control) is sufficient to compare proportional differences in pipe sharing at 90% power with significance of *p* = 0.05. We assume 52% will share pipes, and that there will be a difference of 20% (52% to 32%) between control and intervention; substantiating previous evidence suggesting pipe provision reduces prevalence of sharing from 37 to 12% over a 6 month period [16]. An inflated sample of 740 (500 SIPP, 240 control) allows for linkage of 75% of participants between baseline and follow-up surveys and for multivariable analyses to adjust for any baseline differences in characteristics between intervention and control sites (see Fig. 3).

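### The dose–response analysis names only logistic regression, which does not fit the two secondary outcomes defined as counts: injections and days sharing pipes

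*Protocol article*

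**What the plan says.** The fourth analysis under Impact evaluation, Analysis, relates the intensity of exposure to "primary and secondary outcomes using logistic regression models", "categorising exposure to SIPP as a continuous or categorical variable". The suggested bands are 1, 2–3, 4–5 and 6 or more contacts. Logistic regression is the only model named. No outcome is exempted and no cut-point is given.

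Outcome measures defines most secondary outcomes as yes/no items or proportions. Two are quantities over a 28-day recall period: how many times the person injected, and on how many days they shared pipes.

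For the between-arm comparison, the same Analysis section does treat injecting as a quantity: "Linear regression models will compare baseline frequency of injecting between intervention and control sites" and will "estimate relative changes in mean frequency of injecting". It adds that "Logistic and linear models will adjust for a priori confounders", so both model families are in use there. The outcomes placed under the common plan are "secondary outcomes (use of homemade pipes, cuts/burns, injecting, and service engagement". Days sharing pipes is not in that list, and the article gives it no model other than logistic regression.

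**The concern.** A binary logistic model needs a yes/no response. To follow the dose–response sentence as written, the analyst must cut both counts at a point the article does not state. Any cut discards information on frequency, which is what these two outcomes were defined to measure.

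The most obvious cut, any versus none, has two specific faults. It cannot register a fall in frequency among people who go on injecting or sharing. And for days sharing it reproduces the primary outcome (any pipe sharing in 28 days) for anyone who answers both questions consistently, so the secondary outcome adds nothing.

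This matters because Study population gives reduced injection frequency as one reason for including people who inject. The sites are also non-equivalent and not randomised, so a gradient with exposure is useful supporting evidence of an effect. A gradient diluted by the choice of model would weaken that evidence for no gain.

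**Working it through.** **1. The plan's own figure.** Sample size states: "A sample of 306 (204 SIPP, 102 control) is sufficient to compare proportional differences in pipe sharing at 90% power with significance of" 0.05, with "We assume 52% will share pipes, and that there will be a difference of 20% (52% to 32"%). Take control p₁ = 0.52, SIPP p₂ = 0.32, allocation r = 2, two-sided 5%, 90% power. The pooled proportion is (0.52 + 2 × 0.32)/3 = 0.3867.

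- Uncorrected control n = [1.960 × √(1.5 × 0.3867 × 0.6133) + 1.282 × √(0.52 × 0.48 + 0.32 × 0.68/2)]² / 0.20² = (1.169 + 0.767)² / 0.04 ≈ 93.7, so 94.
- With continuity correction: (93.7/4) × [1 + √(1 + 2 × 3/(93.7 × 2 × 0.20))]² ≈ 101.1, so 102.
- Total: 102 + 204 = 306, as stated.

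This calculation concerns the binary primary outcome. Nothing in it depends on the dose–response model.

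**2. Outcome type against named model.**

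| Secondary outcome | Type in Outcome measures | Between-arm model | Dose–response model |
|---|---|---|---|
| Injecting frequency | count | linear | logistic |
| Days sharing pipes | count, 0–28 | no non-logistic model named | logistic |
| Homemade pipes, cuts/burns | yes/no | logistic | logistic |

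The mismatch is confined to the first two rows.

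**3. What a cut costs.** The documents give no distribution for either count, so the inputs below are assumptions unless a source is named.

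- n = 375 (75% linkage × 500 SIPP, from Sample size) or 500. All are taken to have some exposure.
- Four equally likely dose levels, x = 0, 1, 2, 3.
- Injecting: 50% with any. Days sharing: 52% with any (the sharing prevalence in Sample size).
- Among those with any event, Y = 1 + an overdispersed count with mean m₀ × 0.8ˣ. For injecting, m₀ = 40 and k = 1. For days sharing, m₀ = 8 and k = 1.5, capped at 28.
- The 20% fall per step applies to that mean. From lowest to highest dose it is multiplied by 0.8³ = 0.512.
- 500 simulated datasets per scenario, tests two-sided at 5%. Simulation standard error is about √(0.47 × 0.53/500) = 2.2 percentage points.

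Models: logit P(Y > c) = α + βx, with c = 0 or c = the median among those with any event; E(Y) = α + βx; and log E(Y) = α + βx. The last two use robust errors.

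Proportion of datasets in which the gradient is detected:

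| Scenario | n | Logistic, any/none | Logistic, median cut | Linear | Robust Poisson |
|---|---|---|---|---|---|
| Injecting, share unchanged | 375 | 3% | 47% | 75% | 76% |
| Days sharing, share unchanged | 375 | 5% | 66% | 79% | 80% |
| Days sharing, share also falls (OR 0.8 per step) | 375 | 63% | 92% | 98% | 98% |
| Injecting, share unchanged | 500 | 5% | 59% | 88% | 88% |
| Days sharing, share unchanged | 500 | 5% | 81% | 91% | 93% |
| Days sharing, share also falls (OR 0.8 per step) | 500 | 80% | 98% | >99% | >99% |

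**4. Range of effect.** A separate set of 800 datasets per scenario used injecting with n = 375, 50% injecting, mean 60 among injectors, k = 1 and the share unchanged. It compared any/none logistic with robust Poisson:

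- no effect: 5.4% and 5.4%
- 15% fall per step: 5% and 51%
- 20%: 4% and 80%
- 25%: 4% and 93%
- 30%: 6% and 99%

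The no-effect line shows that the count model's advantage is not bought with extra false positives under these inputs.

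**The case against.** The strongest reply is that the article fixes no cut-point. An any/none cut is one reading among several, and an ordinal logistic model would also fit the wording. A reader might infer from the 3–5% figures that a real fall in frequency would be missed completely. The documents do not support that. Near-alpha power needs both an any/none cut and a share of people with any event that does not change with dose, and in that setting the result follows from the set-up. Study population also expects transitions away from injecting, which a yes/no model does detect. When the share with any sharing falls as well, any/none logistic reaches 63% at n = 375.

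A second reply is that injecting frequency is not lost to the study, because the between-arm comparison models its mean. This stands for injecting. Days sharing has no such backstop in the text.

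A third is that an article may leave the model for each secondary outcome to a fuller document. That would answer silence. Here a model is named, and it does not fit two of the outcomes it is applied to. The general remark in the same paragraph about choosing appropriate models concerns clustering, not outcome type.

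A reader might also infer that new attendance at services, being a service-level ratio, cannot enter an individual dose–response analysis. Outcome measures rules that out: it plans to link SIPP monitoring records to service client lists using personal identifiers, so individual exposure and attendance could be joined.

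**Conclusion.** The point holds within limits. The dose–response analysis assigns logistic regression to two outcomes that the article defines as counts, and for injecting frequency this is inconsistent with the linear model used in the between-arm comparison. Following it as written forces an unstated cut. That cut lowered power in every scenario tested with an effect, although the gap is small where power is already very high. The size depends entirely on assumed distributions and on equally filled dose groups. The direction does not, because a cut discards information on frequency.

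The consequence is limited to a supporting analysis. The primary outcome, its analysis and the sample of 306 (inflated to 740) are unaffected.

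**What to change.** In the dose–response sentence, restrict logistic regression to the yes/no outcomes. For number of injections and for days sharing pipes, name either a linear model, as already used for injecting frequency between arms, or a log-link count model with robust errors. A binomial model for days out of 28 would also suit days sharing. Use the same exposure terms throughout. The simulations show little to choose between linear and robust Poisson (75% v 76% and 79% v 80% at n = 375), so consistency with the between-arm model is reason enough to prefer linear.

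If the team wishes to keep logistic regression for these two outcomes, the cut-point should be stated in advance and the loss of power accepted.

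The cost is one sentence of analysis wording. No extra data or participants are needed.
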